## Abstract

**Background:**

Depression and poor social support are significant risk factors for coronary heart disease (CHD), and stress and anxiety can trigger coronary events. People experiencing such psychosocial difficulties are more likely to be physically inactive, which is also an independent risk factor for CHD. Resilience training can target these risk factors, but there is little research evaluating the effectiveness of such programs. This paper describes the design and measures of a study to evaluate a resilience training program (*READY*) to promote psychosocial well-being for heart health, and the added value of integrating physical activity promotion.

**Methods/Design:**

In a cluster randomized trial, 95 participants will be allocated to either a waitlist or one of two intervention conditions. Both intervention conditions will receive a 10 × 2.5 hour group resilience training program (*READY*) over 13 weeks. The program targets five protective factors identified from empirical evidence and analyzed as mediating variables: positive emotions, cognitive flexibility, social support, life meaning, and active coping. Resilience enhancement strategies reflect the six core Acceptance and Commitment Therapy processes (values, mindfulness, defusion, acceptance, self-as-context, committed action) and Cognitive Behavior Therapy strategies such as relaxation training and social support building skills. Sessions include psychoeducation, discussions, experiential exercises, and home assignments. One intervention condition will include an additional session and ongoing content promoting physical activity. Measurement will occur at baseline, two weeks post intervention, and at eight weeks follow-up, and will include questionnaires, pedometer step logs, and physical and hematological measures. Primary outcome measures will include self-reported indicators of psychosocial well-being and depression. Secondary outcome measures will include self-reported indicators of stress, anxiety and physical activity, and objective indicators of CHD risk (blood glucose, cholesterol [mmol·L^-1^], triglycerides, blood pressure). Process measures of attendance, engagement and fidelity will also be conducted. Linear analyses will be used to examine group differences in the outcome measures, and the product of coefficients method will be used to examine mediated effects.

**Discussion:**

If successful, this program will provide an innovative means by which to promote psychosocial well-being for heart health in the general population. The program could also be adapted to promote well-being in other at risk population subgroups.

**Trial registration:**

ACTRN12608000017325.

## Background

### Psychosocial Risks for Coronary Heart Disease

There is strong and consistent evidence of a causal association between both depression and social isolation or lack of quality social support, and the causes and prognosis of coronary heart disease (CHD) [1]. Acute life-event stress can trigger coronary events [1,2], and anxiety can be involved in the onset of CHD [3]. Poor psychosocial functioning may impact on cardiovascular health via biological mechanisms such as cortisol hypersecretion and disturbed hypothalamic-pituitary-adrenal axis functioning, hypertension and blood pressure reactivity to stress, impaired endothelial and vascular functioning, pro-inflammatory cytokines, platelet aggregation and activation and impaired fibrinolysis, atherogenic lipid profiles, and the development of metabolic syndrome [2,4].

### Resilience Training to Improve Psychosocial Well-being and Promote Heart Health

Identifying effective interventions to reduce depression, stress and anxiety, and improve social connectedness is therefore, a potential means of preventing and managing CHD. Resilience training targets modifiable intra-personal skills and protective factors so as to increase an individual's hardiness for remaining psychologically and physically healthy (i.e., resilient) in the face of cumulative stress. Five key psychosocial protective factors are (a) positive emotions, (b) cognitive flexibility, (c) life meaning, (d) social support, and (e) active coping strategies [5]. Each of these factors has been related to lower levels of depressive symptomatology, lower risk of CHD, and better health outcomes for those already diagnosed with CHD [5,6].

Most resilience studies explore the personal characteristics associated with effective coping or resilience, and focus on young people or individuals experiencing specific adverse circumstances (e.g., illness, bereavement, abuse). There are very few controlled studies investigating resilience training with adults. A worksite trial of a 5 × 8 hour program, implemented over five weeks, demonstrated significantly higher levels of self esteem, locus of control, purpose in life, and interpersonal relations among program participants compared with a control group [7]. A trial of an adaptation of this program with 10 × 90 minute modules, implemented over five weeks, for people with diabetes found no significant difference between program participants and a usual care group on measures of the same psychosocial outcomes or physiological health, although there was some suggestion of improved diabetes-related coping [8]. Participants of a worksite trial of an (approximate) 14 day program, implemented over six months, for employees with illnesses attributed to work stress demonstrated higher levels of effective coping (including seeking social support) and lower levels of depression compared with baseline [9]. While there are many studies examining stress management as part of cardiac rehabilitation [10], we are not aware of any studies that have used resilience training to promote heart health.

### Integrating Physical Activity Promotion with Psychosocial Resilience Training for Heart Health

People experiencing psychosocial difficulties, such as depression, social isolation and life stress, are also likely to be physically inactive [11,12], which is an independent risk factor for CHD [13,14]. Epidemiological evidence suggests at least a 30% median risk reduction in cardiovascular disease for those doing regular activity [15], and it has been estimated that for every 1% increase in population levels of physical activity, up to 100 deaths from CHD could be avoided [16]. Physical activity can also reduce cardiovascular risk factors such as hypertension, hyperlipidaemia, and obesity [15]. Physical activity promotion is therefore, an important component of heart health programs.

Physical activity has also been identified as a potential coping resource [5] that can provide enduring resilience to stress [17]. There are numerous studies indicating a positive association between physical activity and psychosocial well-being [18-20]. Physical activity can protect against incident depression symptoms [21-23], and meta-analyses of treatment studies indicate large effect sizes (-0.8, -1.3) for depression symptoms [20,24]. This evidence provides a justification for integrating physical activity promotion with interventions promoting psychosocial well-being.

Authors of other resilience studies have discussed a possible positive association between resilience training and physical activity. Qualitative feedback from the Waite et al., program indicated that some program participants commenced a fitness regime, even though exercise was not directly covered by the training [7]. Although Bradshaw et al., found no significant group difference for self reported exercise, program participants were significantly less likely than those in the control group to report barriers to physical activity, or trouble exercising because of not liking exercise or health problems [8]. It is not clear however, to what extent physical activity was specifically promoted during this program, although it is likely to have been identified as part of diabetes management. The added value of promoting physical activity as part of resilience training is therefore unclear.

### Aim

We have developed a psychosocial resilience training program (*READY*: REsilience and Activity for every DaY) that promotes psychosocial well-being in adults. The aim of this paper is to describe the design and measures of a study to investigate whether the program can improve psychosocial functioning and lower CHD risk indicators, and the added value of integrating physical activity promotion.

## Methods/Design

### Study Design

Figure 1 provides an overview of the study process. This is a cluster randomized trial with two intervention conditions and a wait list group. Participants in one intervention condition will receive the psychosocial resilience training program (*READY*). Participants in the other intervention condition will also receive the resilience training program, as well as additional content promoting physical activity. Measurements will take place at baseline, two weeks post intervention and after an additional eight weeks, and will include questionnaires, pedometer step logs, physical measures and hematological data. The study protocol was approved by The University of Queensland Medical Research Ethics Committee (2007000303).

**Figure 1 F1:**
[figure not shown]
**Overview of study process**.

### Setting

The study will take place in Townsville, Australia. Townsville is a regional city in the state of Queensland with a population of approximately 175,550 people. Compared with the state of Queensland, the median age of residents (33 years) is younger, the median household income is slightly higher, and the unemployment rate is comparable [25].

### Participants and Randomization

Participants will be volunteers recruited from staff of the Townsville district of the State Government Department of Education and Training. The study will be advertised using information sessions and email lists, and potential participants will submit a written expression of interest. Respondents will be initially screened over the telephone by a research assistant to exclude those who (a) are currently receiving psychiatric/psychological treatment (counseling or pharmacological) or who have previously been diagnosed with a major psychiatric disorder (e.g. schizophrenia), or (b) have a medical condition which contraindicates physical activity participation as suggested by the 2005 Sports Medicine Australia screening guidelines [26].

Eligible respondents will be provided with study details, and those who provide verbal consent will be scheduled for baseline assessment. Participants attending baseline assessment will receive written and verbal information on the study requirements and asked to provide written consent before any data are collected. After baseline assessment, participants will be clustered by occupation (teachers/teacher aides, management/senior staff, administration/support staff) and geographical location (Townsville City, Regional). Each cluster will be randomly allocated to one of the three study conditions by a research assistant simultaneously drawing clusters and conditions out of two separate containers.

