### Sample Size

The sample size is based on detecting a difference in personal well being as measured by Ryff's Scales of Psychological Well-Being [27]. Previous research showed that differences of 3.0 points (SD 4.0) can be detected post intervention [28]. To achieve a similar difference, using a two tailed test with alpha level 0.05 and power of 80%, we will require 28 participants in each of the three groups. Allowing for attrition, we will aim to recruit 30-35 participants per condition.

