Mid Program Review Resilient and non resilient characteristics, activating and trouble shooting coping strategies.	Active coping
Life Values and Meaningful Action About values, value identification, meaningful action.	Life meaning
Social Connectedness Types of support, support responses, active and reflective listening, barriers to social connectedness.	Social support
Relaxation and Pleasant Activities Active relaxation exercises, progressive muscle relaxation exercises, pleasurable activities.	Positive emotions
Review and Planning for the Future Resilient and non resilient characteristics, activating and trouble shooting coping strategies.	Active coping

Note. Although different themes are identified for each session, the content in each session is referred to and followed up in subsequent sessions, so as to integrate the material across sessions.

The program will be implemented as 10 × 2.5 hour sessions over 13 weeks (one school term and two weeks of school holidays). Sessions will be in a group format with 10-20 participants per group, and will be led by an experienced psychologist. A detailed trainer's manual has been prepared including learning objectives, outlines, learning activities, handouts and audiovisual materials for each session. Interventionists will be trained by the program authors (NB and KP).

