There are some methodological issues to consider with this study. Recruitment of staff from a regional district of a government department may result in a study sample that is not representative of the general population. As participants will be recruited from within one organization, there may be a risk of contamination between intervention conditions if they communicate with each other. However the clustering of individuals by occupational group and geographical location may reduce this risk. Participants receiving the physical activity promotion will receive one more intervention session than those who receive only the psychosocial resilience training. It is unlikely however, that the additional two and a half hour session, in the context of the 25 hour program, will by itself provide marked additional benefits. To minimize potential trainer effects, interventionists will be involved in both group conditions (i.e. resilience training AND resilience training + physical activity promotion).

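### Drawing whole occupation-by-location groups to three arms leaves no arm comparison within a group, so one realised allocation cannot separate treatment from occupation- or location-specific change

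*Protocol article*

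**What the plan says.** Under Participants and Randomization, the article states that after baseline assessment "participants will be clustered by occupation (teachers/teacher aides, management/senior staff, administration/support staff) and geographical location (Townsville City, Regional"). It continues: "Each cluster will be randomly allocated to one of the three study conditions". The mechanism is a manual draw carried out by one member of the research staff, described as "simultaneously drawing clusters and conditions out of two separate containers". The article gives no number of clusters, no subdivision of the occupation-by-location groups, and no matching or restriction on the draw. The overview figure is not available to this review.

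The abstract says that "95 participants will be allocated to either a waitlist or one of two intervention conditions". The Sample Size section asks for 28 per group and aims to recruit 30-35 per condition. The intervention section states "Sessions will be in a group format with 10-20 participants per group" and places the programme "over 13 weeks (one school term and two weeks of school holidays").

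The only reason given for clustering is contamination. The Discussion says that "the clustering of individuals by occupational group and geographical location may reduce this risk".

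**The concern.** Occupation and location would normally be balancing factors. Here they define the units that are randomised. If there is one unit per occupation-by-location cell, each arm consists of a few whole categories of employee, and no category appears in more than one arm.

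That matters because the trial measures change in well-being, depression, stress and anxiety across a school term and holidays. Teachers, senior staff and administrative staff could plausibly follow different courses over that calendar, although the article gives no data on this. If they do, a difference between a READY arm and the wait list could reflect who was in each arm, and every between-arm outcome is exposed. The allocation unit cannot be changed once the draw is made.

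**Working it through.** **The plan's own figure.** Inputs from Sample Size: difference 3.0, SD 4.0, two-sided alpha 0.05, power 80%. n per group = 2 × (1.960 + 0.842)² × 4.0² / 3.0² = 2 × 7.85 × 1.78 = 27.9, so 28. The stated figure reproduces. The formula treats participants as independent and says nothing about how they are grouped.

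**Number of clusters (inferred).** 3 occupations × 2 locations = 6. With 95 participants that is 95/6 = 15.8 per cluster on average, which sits inside the stated training-group size of 10-20. The inference fits the article's figures but is not confirmed by it.

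**Can the arms have the same occupational mix?** Each occupation has two cells, one per location, and there are three arms. Two cells cannot be present in three arms, so every occupation is absent from at least one arm. This holds for any split and any cell sizes. Enumeration agrees:
- Two cells per arm: 6!/(2!2!2!) = 90 allocations; equal occupational mix in 0.
- Any split with no empty arm: 3⁶ − 3 × 2⁶ + 3 = 540 allocations; equal occupational mix in 0.

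**How uneven are the draws with two cells per arm?** The six cells form 15 pairings, each assignable to arms in 6 ways.
- 8 pairings contain no same-occupation pair, so (15 − 8) × 6 = 42 of 90 draws (47%) leave an arm with a single occupation.
- 6 pairings join one City cell to one Regional cell in every arm, so location balances in 36 of 90 (40%) and 54 of 90 (60%) leave an arm with a single location.
- 2 pairings meet both conditions (12 draws), so 78 of 90 (87%) have a single-occupation arm, a single-location arm, or both.

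**Can adjustment repair it?** At cluster level, an additive model needs an intercept, 2 arm terms, 2 occupation terms and 1 location term: 6 parameters for 6 clusters. By the rank of the design matrix over the 90 draws:
- 48 draws: both arm contrasts estimable, with 0 residual cluster degrees of freedom.
- 36 draws: only one contrast estimable.
- 6 draws: neither, because arm coincides with occupation.

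If the occupation-by-location interaction is also allowed, arm cannot be separated in any draw, because each cell is in one arm.

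**Arm size.** Two equal cells per arm would give 95/3 = 31.7 per arm, within the 30-35 target. The article gives no occupational or geographic split. As an illustration only, assume 60/15/25 by occupation and 75/25 by location. The cells are then about 42.8, 14.3, 10.7, 3.6, 17.8 and 5.9. The smallest pair totals 9.5 and the largest 60.6. The target is met only if cell sizes happen to be favourable.

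**The case against.** The strongest reply is that the draw is random. Over repeated allocations the estimate is unbiased, and each cluster lying in one arm is simply what cluster randomisation means. Both points stand. A reader might infer from the design that the comparison is systematically biased; the article does not support that. The weakness is that there are so few and such broad units that the single realised allocation must be uneven.

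Second, outcomes are measured at baseline and modelled over time, which deals with stable differences in level between staff groups. That also stands. What remains is differential change, and the article neither shows nor excludes it.

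Third, six clusters and two per arm are inferences. If cells were subdivided before the draw, for instance into training groups, the counts do not apply. Without the two-per-arm restriction it is also wrong to say that every arm must lack an occupation: that holds in 324 of 540 splits, because an arm with three or more cells can contain all three. Nor is every arm always a different kind of employee on each factor taken singly. With two cells per arm, two arms share an occupational mix in 36 of 90 draws and location balances in 36 of 90. The result that no draw gives all three arms the same occupational mix needs only one cluster per cell.

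Fourth, one might infer that the clustering gives no protection against contamination. The Discussion claims only a possible reduction, and keeping colleagues of the same occupation and location together does provide some. The protection is partial, because staff of different occupations at one site can be drawn to different conditions.

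**Conclusion.** The concern holds, conditional on the natural reading of one cluster per occupation-by-location cell. On that reading no within-cell comparison of arms exists, equal occupational mix across arms is impossible, and covariate adjustment either loses a contrast (42 of 90 draws) or uses up all cluster-level information (48 of 90). The percentages further assume two cells per arm and equally likely draws.

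The consequence is that the realised trial could not distinguish a programme effect from occupation- or location-specific change over the term and holidays. Whether such differential change is large is unknown from the article. The Analyses section names no adjustment for occupation or location; that may be left to the full plan and is not the criticism, since the adjustment would not cure the problem. The 30-35 per condition target is also not controlled by the procedure described.

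**What to change.** After baseline, randomise whole schools or worksites to the three conditions, with all volunteers at a site kept together whatever their occupation. Stratify by location, and constrain or minimise the allocation on occupational mix and number of volunteers per site. In the analysis, include occupation and location as fixed effects and worksite as a random effect. Occupations can then appear in every arm, and colleagues at one site share a condition.

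If smaller clusters were already intended, Participants and Randomization should define them and use occupation and location as balancing factors.

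Cost: allocation already follows baseline assessment, so recruitment need not change, but worksite must be recorded before the draw. Training groups would mix occupations and may combine sites to reach 10-20 people, and some contact between sites remains. The article does not say how many worksites would contribute volunteers, so that must be checked first.

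The stated power must also allow for a design effect, 1 + (m − 1) × ICC, with m the volunteers per site. No ICC is given. For scale, at the 15.8 per cluster implied by six clusters, assumed ICCs of 0.01, 0.02, 0.05 and 0.10 give design effects of 1.15, 1.30, 1.74 and 2.48, raising 28 per arm to 33, 37, 49 and 70. Smaller worksite clusters would need less inflation at the same ICC.

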### Sample Size

The sample size is based on detecting a difference in personal well being as measured by Ryff's Scales of Psychological Well-Being [27]. Previous research showed that differences of 3.0 points (SD 4.0) can be detected post intervention [28]. To achieve a similar difference, using a two tailed test with alpha level 0.05 and power of 80%, we will require 28 participants in each of the three groups. Allowing for attrition, we will aim to recruit 30-35 participants per condition.

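### The 28 per group is a calculation for independent individuals, so the stated 80% power is not supported for a trial that randomises whole clusters

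*Protocol article*

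**What the plan says.** Study Design states: "This is a cluster randomized trial with two intervention conditions and a wait list group". Participants and Randomization fixes the unit of allocation: "Each cluster will be randomly allocated to one of the three study conditions". It defines the clusters thus: "participants will be clustered by occupation (teachers/teacher aides, management/senior staff, administration/support staff) and geographical location (Townsville City, Regional"). It states no number of clusters.

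Sample Size rests on Ryff's well-being scales, one of the two primary outcome measures. It cites earlier research in which "differences of 3.0 points (SD 4.0) can be detected post intervention", and sets the requirement "using a two tailed test with alpha level 0.05 and power of 80"%. The result is "we will require 28 participants in each of the three groups". The margin above 28 is assigned to dropout: "Allowing for attrition, we will aim to recruit 30-35 participants per condition". The section gives no intracluster correlation (ICC), cluster size, cluster count or design effect.

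In the Discussion, clustering appears only as something that may limit contamination between conditions.

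**The concern.** When intact groups are randomised, members of a group tend to resemble each other, and the between-cluster variance enters the treatment comparison. Here the clusters are defined by job type and location, so some similarity in well-being is plausible. A sample size that treats every participant as independent then overstates power unless the ICC is zero.

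This is not a detail that a condensed article has left to a fuller document. If 28 is already the complete result of the independent-individuals formula, no inflation for clustering can be hidden inside it. An analysis plan could choose a model that handles clustering properly, but that would not make the stated 28 a calculation for a cluster design.

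At stake is the interpretation of a primary outcome. Readers told that the trial had 80% power for 3.0 points could give a null result more weight than the design can bear.

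**Working it through.** **Inputs from the protocol article.** Difference 3.0, SD 4.0, two-sided alpha 0.05, power 80%, 28 per group, 30–35 recruited per condition (Sample Size); 95 participants in total (Abstract); three occupation categories and two locations (Participants and Randomization).

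**Inputs assumed.**
- ICC 0.01 to 0.10; none is given.
- Six clusters, from 3 × 2 fully crossed; inferred, not stated. This means about two per arm, each of m = 28/2 = 14.

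**Step 1: reproduce the stated figure.** For independent individuals,

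n = 2 × (z₀.₉₇₅ + z₀.₈₀)² × (SD/difference)² = 2 × (1.96 + 0.8416)² × (4.0/3.0)² = 27.9, rounded up to 28.

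The match is exact with a design effect of 1. Normal-approximation power at 28 is 80.1%, so there is no slack. With other conventions the figure does not match: one-sided 22, exact t 29, Bonferroni for two comparisons 34, for three 38.

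**Step 2: allow for clustering, normal quantiles.** Design effect DE = 1 + (m − 1) × ICC = 1 + 13 × ICC. Standard error of the difference SE = 4.0 × √(2 × DE/28). Power ≈ Φ(3.0/SE − 1.96).

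| ICC | DE | SE | 3.0/SE | Power |
|---|---|---|---|---|
| 0 | 1.00 | 1.069 | 2.81 | 80% |
| 0.01 | 1.13 | 1.136 | 2.64 | 75% |
| 0.05 | 1.65 | 1.373 | 2.18 | 59% |
| 0.10 | 2.30 | 1.621 | 1.85 | 46% |

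**Step 3: sensitivity to few clusters.** If the test uses cluster-level degrees of freedom with variance pooled over the three arms, df = 6 − 3 = 3. Power then comes from the non-central t distribution with non-centrality 3.0/SE.

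| ICC | Power for 3.0 points, 3 df | Difference detectable with 80% power, 3 df |
|---|---|---|
| 0 | 48% | 4.5 |
| 0.01 | 44% | 4.8 |
| 0.05 | 33% | 5.8 |
| 0.10 | 26% | 6.9 |

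**Step 4: can the recruitment margin absorb it?** Recruiting 30 to 35 covers a design effect of at most 30/28 = 1.07 to 35/28 = 1.25, and only with no dropout. The table keeps two clusters per arm, retains everyone, uses normal quantiles, and sets m to half the arm size.

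| Per arm | ICC 0.01 | ICC 0.05 | ICC 0.10 |
|---|---|---|---|
| 31.7 (95/3) | 79.5% | 62% | 47% |
| 35 | 83% | 64% | 49% |

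**The case against.** Four points can be made on the other side.

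**The size of the loss is assumed.** The article states neither an ICC nor a cluster count, and Analyses names random effects mixed modelling without fixing a degrees-of-freedom method. This stands. The 3-df figures, including 48% at ICC 0, show the cost of one possible test, so they are a sensitivity analysis and not a property of the stated plan. More clusters than six would shrink the loss. They would not remove it at 28 per group, given a positive ICC and more than one person per cluster.

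**Baseline data could recover power.** The planned model includes the baseline measurement. If SD 4.0 is a raw-score SD (not stated), adjustment for a baseline correlation r multiplies the variance by about 1 − r². On normal quantiles a design effect DE is offset when r = √(1 − 1/DE): 0.34 for 1.13, 0.63 for 1.65 and 0.75 for 2.30. This also stands, and it is why a reader should not infer that the trial is certain to have less than 80% power. The documents do not support that stronger reading. Sample Size, however, gives no correlation and claims no gain, so it cannot rest its 80% on one. Nor would moderate adjustment suffice under 3 df: at ICC 0.01 and r = 0.4, power is about 50%.

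**The margin above 28 might cover a small ICC.** At 35 per arm, ICC 0.01 and no dropout it would (83%). But the article assigns that margin to attrition, and it does not cover an ICC of 0.05.

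**Individual randomisation might rescue the calculation.** A reader might infer that, if allocation moved to individuals within occupation-by-location strata, the individual formula would apply with 29 per group by the t distribution. The documents do not support this. The Intervention section delivers the programme in groups of 10–20, so outcomes in both intervention arms can remain correlated by delivery group. Assume 29 per arm in groups of about 14.5, so DE = 1 + 13.5 × ICC, which is 1.675 at ICC 0.05. Normal-quantile power is then about 69% against the waitlist (variance 4.0² × (1.675 + 1)/29) and about 60% between the two intervention arms (variance 4.0² × 2 × 1.675/29). The Discussion also relies on clustering to limit contamination within one employer.

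**Conclusion.** The point holds in this form: the 28 per group is arithmetically correct for independent individuals, but it is not a calculation for the cluster design described, so the 80% claim is unsupported. That mismatch follows from the article alone. So does the direction: on the section's own inputs, any positive ICC takes power at 28 per group below 80%.

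The size is conditional. With six inferred clusters and assumed ICCs of 0.01 to 0.10, power is about 75% down to 46% on normal quantiles, before any gain from baseline adjustment. The sensitivity analysis with few degrees of freedom gives about 44% down to 26%. None of these figures is the trial's known power. The paragraph should be corrected, because it is the only justification given for the sample size.

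**What to change.** Rewrite the Sample Size paragraph so that it matches the unit of randomisation. It should state:

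- the number of clusters, and their expected size and distribution over the three conditions;
- an assumed ICC as a range, with its basis;
- the design effect 1 + (m − 1) × ICC;
- the degrees of freedom used for the test;
- any baseline correlation relied on, and whether SD 4.0 is a raw or an adjusted SD;
- the resulting power for 3.0 points, or the difference detectable with 80% power.

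Withdraw the unqualified 80% claim. Do not replace 28 with an individual-level figure such as 29, even if allocation changes, unless correlation within delivery groups is also allowed for.

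The cost is one rewritten paragraph and a less favourable stated power. No extra participants are needed for this correction. It discloses the trial's precision and does not restore the power.
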